## Methods/design

The study was designed as a prospective, parallel group, single-blinded, randomized controlled clinical trial. The study protocol was written in accordance with the Standard Protocol Items: Recommendations for Interventional Trials (SPIRIT) guidelines (Additional file 1 shows the SPIRIT checklist). The trial has been registered in both English and Chinese at chictr.org.cn (ChiCTR1900025538) on August 31, 2019. The flowchart of the study design is shown in Fig. 2 and a detailed schedule of enrolment, intervention, and assessment is given in Fig. 3.

**Fig. 2 Fig2:**
[figure not shown]
Trial flow chart

**Fig. 3 Fig3:**
[figure not shown]
Schedule of enrolment, intervention, and assessment

### Study site

All assessments will be conducted within the Diabetic Foot Care Center, Department of Endocrinology and Metabolism, West China Hospital, Sichuan University, Chengdu, Sichuan, People’s Republic of China. Our Diabetic Foot Care Center is one of largest multidisciplinary care centers in China with a database of more than 2500 patients with a history of DFU. Therefore, we would be able to recruit adequate eligible participants.

### Participants

Patients with a history of DFU whose healing time of foot ulcer was over 3 months will be invited to participate in our trial by phone. Individuals will be eligible for the trial if they meet the following inclusion criteria: (1) aged ≥ 18 years, (2) type 1 diabetes (T1DM) or type 2 diabetes (T2DM), (3) decrease or loss of protective foot sensation due to/as a result of diabetic peripheral neuropathy, and (4) had a healed foot ulceration in the 3 months prior to randomization. However, individuals will not be enrolled into this trial if they meet the following exclusion criteria: (1) amputation proximal to the tarsometatarsal joint, (2) the use of walking aids that offload the foot, (3) severe lower extremity artery disease (ankle brachial index ≤ 0.4, intermittent claudication or rest pain), (4) osteoarticular diseases unrelated to T1DM or T2DM, (5) decrease or loss of vision that is difficult to treat or correct, (6) unstable cardiovascular disease or unstable ischemic cerebrovascular disease, (7) severe renal dysfunction (estimated glomerular filtration rate (eGFR) < 30 mL/min per 1.73 m^2^) or severe liver dysfunction (Child-Pugh grade C), (8) malignant tumor, (9) severe illness that would make 24-month survival unlikely (as judged by the patients physician), (10) pregnancy or breast-feeding women, (11) neurologic or psychiatric disease that may prevent compliance with the protocol, and (12) patients who are considered unsuitable for the trial by investigators.

Potential participants will be given a brief verbal explanation of the trial by their treating podiatrist. Research assistants will give them telephone interviews and invite patients who are willing to participate to our diabetic foot center for further confirming eligibility and baseline measurements. Written informed consent will be obtained by a trained and experienced podiatric nurse or podiatrist at the baseline visit. On the consent form, participants will be asked whether they agree to use of their data and biological specimens when they choose to withdraw from the trial and asked for permission for the research team to share their relevant data with people from the universities taking part in the research or from the regulatory authorities.

### Sample size calculation

PASS 11.0 software was used to obtain sample size. As a parallel-group randomized controlled trial, the Log-rank Test (Lakatos) was used for the sample size calculation based on the following parameters or assumptions:
The survival probability of treatment group was estimated for 77.9%. According to the latest national multicenter survey data in China, 31.6% patients with a history of DFU developed new ulcer during 1 year follow-up [5]. Thus, the survival probability of control group was assumed to be 64.8%. We assume that the treatment group could have a 30% higher survival probability than control group.The accrual period for patients’ recruitment was estimated for 12 months. The accrual pattern would be equal. The follow-up period would be 12 months. Therefore, the total time of this trial would last 24 months.The power was set at > 0.8, while *α* was 0.05. The dropout rate of 0.2 was assumed. No switching between two groups. Two groups would have same sample size.

Therefore, the total sample size calculated using PASS was at least 314 cases. In this trial, we would recruit a total of 320 patients (160 for each group).

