## Background

The development of foot ulcers is a significant marker of the extent of long-term complications in patients with diabetes mellitus, which is the most common reason for lower limb amputation [1]. Diabetes-related foot ulcers precede at least 60% of all nontraumatic lower limb amputations [2]. Mortality following amputation ranges from 50 to 68% at 5 years and is worse than that of many forms of cancer [2, 3]. Moreover, even after the resolution of a foot ulcer, recurrence is also common [4, 5]. A recent large cohort study in China showed that the incidence rate for foot ulcer recurrence within 1 year also reached 31.6% [5]. Therefore, prevention of ulcer recurrence or occurrence is of prime importance in the current approach to diabetic foot disease.

DFU is an outcome of a combination of multiple causes including pathophysiologic changes, foot deformities, and trauma [2]. Although pathophysiologic changes such as peripheral neuropathy or/and peripheral arterial disease (PAD) play a central role in the development of foot ulcers, foot deformities contributes directly to foot ulcer occurrence. These deformities as a result of diabetic autonomic and motor neuropathies lead to areas of increased peak plantar pressures, which are common sites of ulceration formation [2]. To reduce ulceration formation, diabetic therapeutic footwear for high-risk patients was widely recommended in clinical practice [6]. Reductions of plantar pressures, shear forces, and friction on the sole of the foot and the toes are primary mechanisms of therapeutic footwear, which are responsible for protecting against foot ulcers [6–16]. Data from observational studies suggested a significant protective benefit from improved custom-made footwear [7–12]. However, in well-designed randomized controlled trails (RCTs), no statistically significant benefit was observed in patients wearing improved footwear compared with those with usual care [13–15]. Based on several published reviews of clinical trials, the discrepancy between observational studies and RCTs might be attributed to characteristics of intervention shoes, adherence to treatment, risk factors for reulceration, and so on [15, 16]. Thus, footwear effectiveness may not only need a function of offloading but also adequate patients’ adherence [14–16].

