### Outcome measures

#### Primary outcome measure

The main study outcome measure is the incidence of ulcer recurrence. Ulcers are defined as cutaneous erosions through the dermis that may extend to involve the subcutaneous tissue or even to the level of muscle or bone [27, 28]. We expect at least a 30% reduction in the incidence of ulcer recurrence from baseline to the end of intervention.

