### Statistical analysis

At the end of this trial, all original data without participants’ name and the random sequences will be sent to a statistician for data analysis. Statistical analysis will be performed using SAS version 9.4 (SAS Institute Inc., Cary, NC, USA). Significance level will be set at *α* = 0.05. Quantitative variables expressed as means ± standard deviation or median with interquartile range, and categorical data will be recorded as numbers and percentages. Between-group differences of continuous variables will be tested for significance using Student *t* test when original data or data via transformation of variables is normally distributed or using Wilcoxon rank-sum test when data is not normally distributed. A chi-square test will be used for categorical data.

The primary end point, ulcer recurrence, will be analyzed according to the intention-to-treat principle, with event curves for the time to the first event on the basis of Kaplan–Meier analysis, and treatments will be compared by means of the log-rank test. A cox regression model will be used to calculate the hazard ratio for the primary end point. Among secondary end points, plantar pressures at baseline and at 3, 6, 9, and 12 months will be compared with repeated measures ANOVA. The changes blood flow parameters of lower extremity at baseline and at 12 months will be compared using Student *t* test when these means between groups are comparable at baseline or using analysis of covariance (ANCOVA) when these means are not equivalent at baseline. For cardiovascular events, the hazard ratio for the comparison of treatment group with control group and 95% confidence intervals will be estimated with the use of a proportional-hazards model.

The footwear adherence will be calculated for each group and then ulcer recurrence rates will be compared between the subgroups of patients with high adherence and low adherence by *χ*^2^ tests. We also plan to explore whether potentially important covariates such as age, sex, body mass index, physical activity, and diabetic duration could potentially confound the results.

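### The control-arm survival of 64.8% contradicts the cited 31.6% recurrence (which gives 68.4%) and drove the sample size, so 320 patients give about 56% power, not more than 80%

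*Protocol article*

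**What the plan says.** All statements are in the Protocol article.

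- Sample size calculation, source of the control rate: "31.6% patients with a history of DFU developed new ulcer during 1 year follow-up". The Background gives the same figure: "the incidence rate for foot ulcer recurrence within 1 year also reached 31.6" per cent.
- Sample size calculation, control arm: "Thus, the survival probability of control group was assumed to be 64.8" per cent.
- Sample size calculation, treatment arm: "The survival probability of treatment group was estimated for 77.9" per cent.
- Sample size calculation, effect: "We assume that the treatment group could have a 30% higher survival probability than control group".
- Primary outcome measure, effect: "We expect at least a 30% reduction in the incidence of ulcer recurrence from baseline to the end of intervention".
- Sample size calculation, power: "The power was set at > 0.8". The other settings are alpha 0.05, dropout 0.2, equal arms, even accrual over 12 months, 12 months of follow-up and 24 months in total. The result is at least 314 patients, with 320 to be recruited.

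**The concern.** The control rate is presented as following from the cited recurrence, and it does not. The treatment rate does follow from that recurrence. Pairing the two widens the assumed gap from 9.5 percentage points (77.9 − 68.4) to 13.1 (77.9 − 64.8), and required sample size is very sensitive to that gap.

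The wording hides the slip, because 77.9% is not 30% higher than either control figure. It corresponds to 30% fewer recurrences than 31.6%, which is the target in the Primary outcome measure section. That section states the reduction as running from baseline, although everyone enters with a healed ulcer and the planned test compares the arms. This is a minor wording point.

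At stake is the power for the only primary endpoint. The Background says that earlier randomised trials of improved footwear found no significant benefit. If this trial has roughly even odds of detecting its own target effect, a null result would tell little, yet the stated power would invite reading it as a real negative.

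**Working it through.** **1. Survival figures**

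- Control survival from the cited recurrence: 1 − 0.316 = 0.684 (stated 0.648).
- Treatment survival with 30% fewer recurrences: 1 − 0.7 × 0.316 = 0.7788, the stated 77.9%.
- Had 64.8% been the intended base, the same 30% reduction would give 1 − 0.7 × 0.352 = 0.754, not 0.779.
- Reduction implied by 64.8% vs 77.9%: 1 − 0.221/0.352 = 37%.
- Survival ratios: 0.779/0.648 = 1.20 and 0.779/0.684 = 1.14. A literal 30% increase would give 0.842 or 0.889.

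**2. Hazard ratios** (exponential, 12-month survival)

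- Stated: ln 0.779 / ln 0.648 = 0.576.
- Corrected: ln 0.779 / ln 0.684 = 0.658.

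**3. Reproducing the stated 314**

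Method: Lakatos log-rank, uniform accrual over 12 months, 24 months in total, 1:1 allocation, alpha 0.05, power 0.80. The article gives neither the sidedness of alpha nor the time base of the dropout. I assumed two-sided and 20% per year in each arm, entered as a hazard.

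- 64.8% vs 77.9%: N = 312 (stated 314); power at 320 is 81%.

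On the stated accrual and follow-up with 64.8%, the alternatives move away from 314: 289 if the 20% loss is spread over 24 months, 268 with no loss, and 246 one-sided. The assumed reading is therefore the best supported.

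**4. With the correct control rate**

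- 68.4% vs 77.9%: N = 569; power at 320 is 56%.

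A hand check by Schoenfeld's formula agrees. Yearly hazards are 0.380 (control), 0.250 (treatment) and 0.223 (loss). With k the sum of event and loss hazards, the probability of an observed event is (λ/k) × [1 − (e^−k − e^−2k)/k], which is 0.371 and 0.266, mean 0.318.

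- Events needed: 4 × (1.960 + 0.842)² / (ln 0.658)² ≈ 179, so N = 179/0.318, about 561.
- Events expected with 320 patients: about 102. Power = Φ(√102/2 × 0.419 − 1.96) = Φ(0.16), about 56%.

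**5. Sensitivity at N = 320, control 68.4%, stated accrual and follow-up**

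| Dropout | Two-sided | One-sided |
|---|---|---|
| 20% per year | 56% | 68% |
| 20% over 24 months | 59% | 70% |
| None | 62% | 73% |

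The smallest N for 80% power in this table is 384 (one-sided, no dropout), still above 320.

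**6. Follow-up as scheduled**

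Study procedures and Follow-up visits end each participant's follow-up at 12 months, whereas the calculation credits early entrants with up to 24. With 12 months fixed, two-sided and 20% yearly loss:

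| Control survival | Power at 320 | N for 80% |
|---|---|---|
| 64.8% | 70% | 410 |
| 68.4% | 45% | 751 |

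The survival slip thus costs about 25 points under either follow-up (81 to 56, or 70 to 45). The rest of the fall to 45% comes from the follow-up mismatch.

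**7. Detectable effect**

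With 68.4% control survival and 320 patients, 80% power needs a recurrence reduction of about 39% on the stated design, or about 45% with 12 months fixed.

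**The case against.** Five points can fairly be made for the plan.

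- *Sidedness and dropout time base are not stated, so 56% is one value in a range.* True. The range on the stated design is 56% to 73%, and 56% is its lower end. It is also the reading that comes closest to 314, and the whole range is below 80%.
- *312 is not 314, and some setting with 68.4% might reach 314.* One comes close: a one-sided test, no dropout and everyone followed for 24 months gives N = 307. It contradicts the protocol's own accrual and dropout assumptions, so it does not explain the stated figure.
- *64.8% may have been deliberate.* The article gives no other basis for it and derives it from 31.6%. Even if it is kept, the planned 30% reduction leads to 75.4% in the treatment arm, N of about 494 and 62% power at 320.
- *A digit swap is only inferred.* That stands. 68.4 turning into 64.8 is the natural explanation but cannot be shown from the text. The contradiction and the loss of power do not depend on it.
- *The 45% mixes two defects.* Also right, which is why the two effects are separated above. The phrase about baseline may simply describe the observation window. The analysis section compares arms by log-rank test and Cox model, so it does not affect the analysis.

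**Conclusion.** The control survival of 64.8% is wrong on the protocol's own figures, and it was the value used to size the trial. For the protocol's stated hypothesis, a 30% reduction from 31.6%, 320 patients give about 56% power on the stated design and about 45% with the 12-month follow-up that is scheduled. Reaching 80% would take about 569 or 751 patients respectively.

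These figures assume exponential event times, a two-sided 0.05 test and 20% loss per year. Other readings of sidedness and dropout on the stated design give up to 73%. No reading consistent with the stated accrual and follow-up supports the claim of more than 80%. This must be corrected, because the protocol's justification of its sample size fails.

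**What to change.** - In the Sample size calculation, replace 64.8% with 68.4%, after the sponsor confirms that 31.6% is the intended base.
- Replace the statement about higher survival with a 30% relative reduction in 12-month recurrence versus control (31.6% to 22.1%), and use the same between-group wording under Primary outcome measure.
- State whether alpha is two-sided and over what period the 20% dropout applies. Set the follow-up in the calculation to what each participant will actually have.
- Rerun PASS and report the power of 320 patients (about 56% on the stated settings, about 45% with 12-month follow-up) and the reduction detectable at 80% power (about 39% or 45%).

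The cost is one software rerun and a wording amendment, and a less favourable power statement. Correcting the statement does not require more patients; whether to enrol more is the sponsor's decision. According to Trial status, recruitment was to start in March 2021, after the article appeared in February 2021, so on those dates the correction could have come before enrolment.

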### Study procedures

All participants will be invited to attend the baseline visit and five further study appointments for 12 months on post-randomization. Data at every visit will be collected in case report forms (CRFs) by the trial team. All data will be entered into a secure database by research assistants (i.e., data collectors). In the current trial and further ancillary studies, there are no plans for collection, laboratory evaluation, and storage of biological specimens for genetic or molecular analysis.

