#### Follow-up visits

Participants will be followed at 1 month (visit 2), 3 months (visit 3), 6 months (visit 4), 9 months (visit 5), and 12 months (visit 6) after randomization. At each visit, the trial team will collect the information including incidence of foot ulcer, footwear adherence, cardiovascular events, glucose profile, and other cardiovascular risk factors control. For physical activity evaluation, participants will be asked to wear a pedometer (P084, SPORTWAY, ShenZhen, China) every day to record the date and steps taken per day. Meanwhile, a concealed activity monitor (Lifecorder Plus, Suzuken) will be attached to the diabetic therapeutic footwear. Activity data will be uploaded by a research assistant to a centralized server via internet at each follow-up visit. Adherence to treatment will be evaluated through the comparison of the step counts recorded by a concealed activity monitor with those recorded by a pedometer. Adherence to treatment will be monitored until the end of follow-up. Plantar pressure distribution patterns will be measured after randomization every 3 months. At the end of follow-up, ABI and blood flow parameters of lower extremities will also be collected. At each visit, if participants make a withdrawal request or are not eligible to continue due to the presence of severe concomitant diseases or conditions listed in the exclusion criteria, they will be discontinued from the study. For participants who drop out, the information including incidence of foot ulcer, footwear adherence, cardiovascular events, ABI (if possible), plantar pressures (if possible), and biochemical parameters (if possible) will be collected.

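### The log-rank sample size is set up for 12 to 24 months of observation, but each participant is followed for 12 months; on a two-sided 0.05 test the power of 320 is about 70%, not above 80%

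*Protocol article*

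**What the plan says.** The sample size section of the protocol article names its method: "the Log-rank Test (Lakatos) was used for the sample size calculation", run in PASS 11.0. The inputs it lists are:

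- Control arm: "the survival probability of control group was assumed to be 64.8" per cent. Treatment arm: "The survival probability of treatment group was estimated for 77.9" per cent. The source is a one-year figure: "31.6% patients with a history of DFU developed new ulcer during 1 year follow-up".
- Accrual over 12 months at an even rate, and then: "The follow-up period would be 12 months. Therefore, the total time of this trial would last 24 months".
- Alpha 0.05 (sidedness not given), power above 0.8, dropout rate 0.2 (time base not given), equal arms.

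The result is: "Therefore, the total sample size calculated using PASS was at least 314 cases". The trial plans 320.

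The conduct sections describe the observation period. Study procedures plans "five further study appointments for 12 months on post-randomization", and Follow-up visits ends the list with "9 months (visit 5), and 12 months (visit 6) after randomization". The abstract gives the same schedule. The primary analysis is time to first ulcer, compared by log-rank test.

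**The concern.** In a Lakatos calculation, an accrual time and a total time together set how long patients are observed. Accrual of 12 months inside a total of 24 means that all patients are watched to month 24 of the trial: 24 months for the first recruit, 12 for the last, 18 on average. The visit schedule stops every participant at month 12 after their own randomization, and no ulcer assessment is planned after that.

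Log-rank power depends on the number of events. If the calculation counts events from a second year that the trial does not observe, the stated power is too high for the primary endpoint. The Background says that earlier randomized trials of footwear found no significant benefit, so another null result from a trial wrongly believed to have over 80% power would be hard to interpret.

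**Working it through.** **Inputs from the sample size section.** Ulcer-free probability at 12 months 0.648 (control) and 0.779 (treatment); N = 320, 160 per arm; uniform accrual over 12 months; total time 24 months; alpha 0.05; dropout 0.2.

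**Assumptions added.** Exponential times; two-sided test; dropout of 20% per year. The last two are varied below.

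**Hazards per year.** Control −ln 0.648 = 0.4339. Treatment −ln 0.779 = 0.2497. Hazard ratio 0.2497/0.4339 = 0.576, log −0.552. Loss −ln 0.8 = 0.2231.

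**Expected events.** With event hazard h, loss hazard l and observation time T, the probability of an observed event is h/(h+l) × [1 − exp(−(h+l)T)].

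- *Staggered, T uniform on 1 to 2 years:* control 0.4094, treatment 0.2659. Events = 160 × (0.4094 + 0.2659) = 108.
- *Fixed, T = 1 year:* control 0.318, treatment 0.199. Events = 160 × (0.318 + 0.199) = 83.

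The difference is 25 of 108 events, or about 23%.

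**Lakatos calculation.** Follow-up is cut into short intervals. In each, d is the proportion having an event, φ the ratio of treated to control patients at risk, and θ the hazard ratio. With γ = φθ/(1+φθ) − φ/(1+φ) and η = φ/(1+φ)², put e = |Σdγ|/√(Σdη). Then N = [(1.960 + 0.842)/e]² for 80% power, and power at N is Φ(e√N − 1.960).

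**The plan's own figure first.** Staggered follow-up gives N = 312 on a fine time grid (305 on monthly steps), within 3% of the stated 314. Power at 320 is 0.81.

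**Fixed 12 months, as the visit schedule has it.** N = 410 for 80% power. Power at 320 is 0.70.

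**Cross-check by Schoenfeld's formula,** power = Φ(½√events × 0.552 − 1.960):

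- Staggered: ½√108.05 × 0.552 = 2.87; Φ(0.91) = 0.82.
- Fixed: ½√82.72 × 0.552 = 2.51; Φ(0.55) = 0.71.

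Freedman's formula gives 0.80 and 0.69. Log-rank simulation with 20,000 runs gives 0.811 and 0.703.

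**Varying the unstated inputs** (Lakatos, 64.8% versus 77.9%):

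| Test | Dropout | N for 80%, staggered | N for 80%, fixed 12 months | Power at 320, fixed |
|---|---|---|---|---|
| Two-sided | 20% per year | 312 | 410 | 0.70 |
| Two-sided | 20% over 24 months | 289 | 390 | 0.72 |
| Two-sided | none | 268 | 370 | 0.74 |
| One-sided | 20% per year | 246 | 323 | 0.80 |
| One-sided | 20% over 24 months | 228 | 307 | 0.81 |

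**The separate control-rate error.** Recurrence of 31.6% leaves 68.4% ulcer-free, not 64.8%. The treatment figure does follow from 31.6%: 1 − 0.7 × 0.316 = 0.779. With 68.4% versus 77.9%, two-sided and 20% loss per year, power at 320 is 0.56 staggered (102 events) and 0.45 fixed (77 events).

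**The case against.** The quoted sentence can be read as harmless: 12 months to recruit plus 12 months for the last participant does make a 24-month trial, and that agrees with the visit schedule. Nowhere does the protocol say that early recruits are observed for two years.

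A reader might go further than the documents allow and infer that 314 can be obtained only with 12 to 24 months of follow-up. It cannot be put that strongly. Neither sidedness nor the time base of the dropout rate is stated, and the close match of 312 needs a two-sided test together with 20% loss per year; with the loss spread over 24 months the staggered two-sided figure is 289. A one-sided 0.05 test with fixed 12-month follow-up gives 307 to 323, also near 314, and on that reading 320 patients have about 80% power. No variant tried returns exactly 314.

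These points limit what can be said about the PASS entries. They do not remove the mismatch. Accrual and total time are listed among the inputs of a method that uses them to set observation time, and the one-sided reading would make both irrelevant. The protocol mentions no one-sided test. Nor does any passage schedule later ascertainment: exclusion criterion 9 refers to 24-month survival but plans no assessment, and the blood-flow measure collected at the end of follow-up is analysed at 12 months.

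It is also fair that the follow-up issue is the smaller of two defects. On its own it costs about 11 points of power (81% to 70%), while the control survival figure on its own costs about 25 (81% to 56%). The two are distinct, and correcting either leaves the other in place.

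**Conclusion.** The point holds in this form: the listed inputs describe a trial with 12 to 24 months of observation, and the conduct sections describe one with 12. On the plan's own survival figures and a two-sided 0.05 test, 320 patients followed for 12 months give power of 70% to 74%, whichever reading of the dropout rate is taken, and 370 to 410 patients would be needed for 80%. The central case, 20% loss per year, is 83 events, 70% power and about 410 patients.

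The mismatch between inputs and schedule is firm. That the staggered model produced 314 is a well-supported inference, not something the protocol states. If a one-sided test was in fact used, the shortfall almost vanishes on the stated survival figures, but the protocol would then have to say so. The 45% figure belongs to the control-survival error combined with this one and should not be attributed to follow-up alone.

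**What to change.** Rerun the calculation with 12 months of observation per participant. State whether the test is one- or two-sided and over what period the dropout rate of 0.2 applies. Correct the control survival in the same run, and restate the power of 320: about 70% on the stated survival figures, about 45% with 68.4% against 77.9% (two-sided, 20% loss per year). This costs wording and a less favourable power statement. Restoring 80% on the stated survival figures would take about 90 more patients (410 − 320).

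Alternatively, change the conduct to match the calculation: record ulcer status for every participant until the last one reaches month 12, through the phone and messaging contacts already planned for retention, and analyse to that common date. This costs extra contacts for early recruits and a revised schedule. It would support about 81% on the stated survival figures but only about 56% with 68.4%, so the control figure must be corrected either way.
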